#### Pediatric halting rules

The pediatric study pauses enrollment if the number of participants with SAEs in any single MedDRA group exceeds rates expected in children with CM. The expected rates were derived from calculating the cumulative probability of stopping when the true rate of the proportion of participants in a specific MedDRA classification group is a given percent (i.e., 25, 30, 40 or 50%). For example, 9 participants out of the first 17 enrolled must have an SAE within a single MedDRA classification group for the study to pause for review. (This will indicate a single important toxicity that should be considered before further enrollments.) A halt is not triggered, however, if of the first 17 enrolled pediatric participants, 9 experience SAEs in different MedDRA classification groups (e.g., 3 participants die, 3 participants have renal failure, and 3 participants have severe thrombocytopenia). High rates of both adverse outcomes and abnormal laboratory values are expected in pediatric CM. Therefore, only single recurring SAEs within a MedDRA classification group will initiate a pause for safety review. The properties for the halting rules were estimated by Monte Carlo simulation with 100,000 replicates. At any halt, the DSMB will review the data and evaluate whether the study should stop due to safety concerns.

Although we will only report SAEs to the regulatory bodies that have a reasonable possibility of being related to the intervention, for the purpose of applying halting rules, all events (deaths, disability, etc.), even if not specifically reported as SAEs related to treatment, will be documented.

### Strategies to improve adherence to interventions {11c}

Participants are directly observed at the time of dosing by clinical research team members. Administration is documented on paper case report forms (CRFs) and entered into the electronic database. All study concomitant medications are administered under direct observation during the first 24 h after DON administration. Concomitant medication taken at home for up to 14 days after DON administration is followed until completion of the dosing schedule, and the stop date will be recorded in CRFs by study staff.

### Relevant concomitant care permitted or prohibited during the trial {11d}

#### Adults

Adult participants receive a premedication dose of the antiemetic ondansetron, 8.0 mg IV, administered 30 min before DON, and repeated 6 h later. Adult participants with uncomplicated malaria receive six doses (twice daily for 3 days) of oral Co-Artem® (a fixed dose combination tablet containing artemether, 20 mg and lumefantrine, 120 mg) for treatment of uncomplicated malaria, per Malawi Ministry of Health guidelines. All adult participants are infused with IV normal saline at 125 mL/h (maintenance) during the 24-h admission. Due to the possible teratogenic effects of DON on fetal development, all adult participants receive male condoms and are advised to use them for a minimum of 2 weeks following DON treatment.

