### Criteria for discontinuing or modifying allocated interventions {11b}

#### Adults

Dose-escalation in cohorts of adult participants halts if more than four of the 10 subjects in a dosing cohort have related grade 2 and 3 adverse events (AEs) or severe adverse events (SAEs), if there are related SAEs within any dose, or if there is an overall pattern of symptomatic, clinical, or laboratory events that the Pharmacovigilance Group within the Division of Microbiology and Infectious Diseases (DMID) or the Data and Safety Monitoring Board (DSMB) considers associated with the study product. The study will stop enrollment and describe findings to the independent safety monitors (ISM) and the DMSB to evaluate future dose escalation. At the end of adult enrollments, all safety data are reported to the DSMB to inform dose ranges to be studied in children with CM. The DMID medical monitor may stop enrollment and/or administration of study product if AEs meeting the halting criteria are reported.

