### Primary endpoints

In adult participants, the primary endpoint is any grade 2 or 3 AE or SAE in the 14 days after DON administration. In pediatric participants with CM, the primary endpoint includes any SAEs at any time within 14 days after DON administration. The list of solicited AEs is based on known AEs from previous DON trials. All other AEs are documented as unsolicited events. AE grading (Tables 2 and 3) was adapted from the National Institute of Allergy and Immunology (NIAID) Division of AIDS (DAIDS) toxicity tables criteria [43].

**Table 2 Tab2:** Toxicity grading scales for adult participants

Parameter	Grade 1	Grade 2	Grade 3
White blood cells (10^3^/μL)	2.0 to 2.39 if normal baseline 35% reduction from baseline, if abnormal baseline	1.5 to 1.99 if normal baseline 50% reduction from baseline, if abnormal baseline	Less than 1.5 if normal baseline 65% reduction from baseline, if abnormal baseline
Hemoglobin (g/dL)			
Healthy male Normal baseline	10 to 10.9	9 to < 10	< 9
Healthy female Normal baseline	9.5 to 10.4	8.5 to < 9.5	< 8.5
Uncomplicated malaria^a^	35% reduction from baseline	50% reduction from baseline	65% reduction from baseline
Platelets (10^3^/μL)	100 to 116 if normal baseline 35% reduction from baseline, if abnormal baseline	50 to 99 if normal baseline 50% reduction from baseline, if abnormal baseline	< 50 if normal baseline65% reduction from baseline, if abnormal baseline
Serum creatinine	1.1–1.3 × ULN	> 1.3 to 1.8 × ULN	> 1.8 × ULN
Serum SGOT	1.25 to < 2.5 × ULN if normal baseline	2.5 to < 5.0 × ULN if normal baseline	≥ 5.0 × ULN if normal baseline
	35% increase from baseline, if abnormal baseline	50% increase from baseline, if abnormal baseline	65% increase from baseline, if abnormal baseline
Diarrhea	3 or more loose stools in 24 h, treated with dietary changes	6 or more loose stools in 24 h requiring IV rehydration for clinical stabilization, resolving within 36 h	≥ 6 loose stools in 24 h requiring IV rehydration for clinical stabilization, not resolving within 36 h
Gastrointestinal bleeding	Coffee ground emesis or positive stool hemoccult or frank bleeding with < 10% decrease in hematocrit/PCV	Coffee ground emesis or positive stool hemoccult or frank bleeding with a ≥ 10% decrease in hematocrit/PCV not requiring transfusion	Coffee ground emesis or positive stool hemoccult or frank bleeding with a ≥ 10% decrease in hematocrit/ PCV requiring transfusion

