Mucositis	Erythema of the mucosa	Patchy pseudomembranes or ulcerations	Confluent pseudomembranes or ulcerations OR mucosal bleeding with minor trauma
Hematuria	Microscopic hematuria	Frank hematuria with normal serum creatinine (within the normal range for age)	Frank hematuria with elevated (outside of the normal range for age) serum creatinine
Nausea	Nausea with decreased oral intake not requiring intravenous rehydration	Nausea with decrease oral intake requiring intravenous rehydration	Inadequate oral fluid and caloric intake with resulting hypotension or weight loss
Vomiting	1–3 episodes in 24 h with no or mild dehydration	4–6 episodes in 24 h or any amount with moderate dehydration requiring intensive intravenous rehydration	> 6 episodes in 24 h or any amount of vomiting resulting in persistent hypotension

*ULN* Upper limit of normal, *SGOT* Serum glutamic-oxaloacetic transaminase

^a^Platelets and hemoglobin are expected to be abnormal in participants with uncomplicated malaria

**Table 3 Tab3:** Toxicity grading scales for pediatric participants

Parameter	Grade 1	Grade 2	Grade 3
White blood cells (10^3^/μL)	2.0–2.39 if normal baseline	1.5–1.99 if normal baseline	< 1.5 if normal baseline
			65% reduction from baseline, if abnormal baseline
	35% reduction from baseline, if abnormal baseline	50% reduction from baseline, if abnormal baseline	
Hematocrit (PCV)	Not applicable as ongoing anemia and need for blood transfusions not unexpected		
Platelets (10^3^/μL)	100–116 if normal baseline	50–99 if normal baseline	< 50 if normal baseline
		50% reduction from baseline if abnormal baseline	65% reduction from baseline, if abnormal baseline
	35% reduction from baseline, if abnormal baseline		
Serum creatinine	35% increase from baseline	50% increase from baseline	65% increase from baseline
Serum SGOT	1.25 to < 2.5 × ULN if normal baseline	2.5 to < 5.0 × ULN if normal baseline	≥ 5.0 × ULN if normal baseline
			65% increase from baseline, if abnormal baseline
		50% increase from baseline, if abnormal baseline	
	35% increase from baseline, if abnormal baseline		
Serum glucose	Not applicable: hypoglycemia during first 72 h of admission with CM is not unexpected and is closely monitored		
Serum lactate	Not applicable: hyperlactatemia during first 72 h of admission with CM is not unexpected and is closely monitored		

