### Secondary endpoints

Secondary endpoints include each element of the composite primary endpoint to investigate dose-related toxicities, as well as serum DON levels used to calculate PK parameters of the drug. Additional secondary endpoints for all participants include PK parameters such as volume of distribution, maximum concentration (*C*_max_), time to maximum concentration (*T*_max_), area under the curve (AUC), clearance, elimination rate constant, and terminal half-life (*T*_½_). Non-compartmental analysis is used for the estimation of PK parameters.

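### Scheduled saline in adults is likely to pre-empt the only criterion separating grade 1 from grade 2 nausea, so first-24-h nausea may be left out of the adult primary endpoint (minor)

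*Protocol article*

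**What the plan says.** All places are in the protocol article.

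- **Infusion.** Relevant concomitant care {11d}, Adults: "All adult participants are infused with IV normal saline at 125 mL/h (maintenance) during the 24-h admission". Participant timeline {13} mentions the same rate, but only for the adults with uncomplicated malaria.
- **Grading.** Table 2, nausea row. Grade 1 is "Nausea with decreased oral intake not requiring intravenous rehydration". Grade 2 is "Nausea with decrease oral intake requiring intravenous rehydration". Grade 3 requires inadequate intake leading to low blood pressure or weight loss.
- **Endpoint.** Primary endpoints: "In adult participants, the primary endpoint is any grade 2 or 3 AE or SAE in the 14 days after DON administration". Secondary endpoints: "Secondary endpoints include each element of the composite primary endpoint to investigate dose-related toxicities".
- **Halting rule.** Criteria for discontinuing {11b}, Adults. The count limb applies if "more than four of the 10 subjects in a dosing cohort have related grade 2 and 3 adverse events" or SAEs. Escalation also halts on any related SAE, or "if there is an overall pattern of symptomatic, clinical, or laboratory events" that the sponsor's pharmacovigilance group or the DSMB considers associated with the product. At the end of adult enrolment, "all safety data are reported to the DSMB to inform dose ranges to be studied in children with CM".
- **Expected toxicity.** Background and rationale {6a} names nausea and vomiting as the effects most often reported in earlier DON trials.

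**The concern.** A toxicity grade defined by the need for a treatment works only if that treatment is not already being given for another reason. Here every adult, or at least every adult with malaria, receives IV saline on schedule during the admission, when nausea after a single dose is most likely to be observed. The infusion can remove the clinical need that would mark grade 2, and nothing else in the nausea row separates the two grades.

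This line is also the entry threshold for the adult primary endpoint. If it moves, three things move with it: the proportion with a primary endpoint event, the nausea component reported by dose as a secondary endpoint, and the number counted towards halting a cohort. Nausea is one of the two toxicities most expected from this drug, so its dose relation is a main thing the adult part should show. The adult part is open-label and has no comparator, so no control rate exists against which a depressed nausea count would stand out.

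**Working it through.** **Step 1. Volume.** 125 mL/h × 24 h = 3,000 mL = 3.0 L per adult. It is scheduled in 80 adults (40 healthy, 40 with malaria) by section {11d}, or in 40 if only the group named in section {13} is infused.

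**Step 2. What separates the grades.**

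| Table 2 row | Grade 1 | Grade 2 | Can grade 2 be reached without IV rehydration? |
|---|---|---|---|
| Nausea | reduced intake, IV rehydration not needed | reduced intake, IV rehydration needed | No |
| Vomiting | 1–3 episodes in 24 h, no or mild dehydration | 4–6 episodes in 24 h, or moderate dehydration needing intensive IV fluid | Yes, by episode count |

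The vomiting row has an anchor that saline cannot affect. Grades 1 and 2 nausea have none. Grade 3 nausea does not depend on IV fluid.

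**Step 3. Where the line acts.** Grade 1 counts in neither the primary endpoint nor the count limb, and grade 2 counts in both. More than four of 10 means at least 5 of 10.

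**Step 4. Illustration.** The article gives no nausea rate, so there is no planned figure to reproduce and every rate below is an assumption.

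- *b* = 0.10: another related grade 2–3 event
- *n* = 0.2, 0.4 or 0.6: related first-24-h nausea with reduced intake
- *f* = 0.5: share of these who would need IV rehydration if no infusion ran
- *m*: share of that true grade 2 nausea recorded as grade 1

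Probability that a participant has a countable event, treating the two sources as independent: p = 1 − (1 − b)(1 − n·f·(1 − m)). The expected count is 10p. The chance that the count limb is met is P(X ≥ 5) for X ~ Binomial(10, p).

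Worked case, n = 0.4:
- m = 0: p = 1 − 0.9 × 0.80 = 0.28
- m = 0.25: p = 1 − 0.9 × 0.85 = 0.235
- m = 0.5: p = 1 − 0.9 × 0.90 = 0.19
- m = 1: p = 0.10

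| Share masked (m) | Expected count of 10, n = 0.2 / 0.4 / 0.6 | Chance count limb is met |
|---|---|---|
| 0 | 1.9 / 2.8 / 3.7 | 3% / 12% / 29% |
| 0.25 | 1.7 / 2.4 / 3.0 | 2% / 6% / 15% |
| 0.5 | 1.5 / 1.9 / 2.4 | 1% / 3% / 6% |
| 1 | 1.0 / 1.0 / 1.0 | 0.2% / 0.2% / 0.2% |

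**Step 5. Sensitivity.** With full masking, if a quarter of nausea cases count anyway through grade 2 vomiting, p = 1 − 0.9 × (1 − 0.25n) = 0.145, 0.19 or 0.235, and the 0.2% rises to 1%, 3% or 6%. The unmasked chances are 1%, 7% and 22% with b = 0.05, and 12%, 27% and 47% with b = 0.20. The matching full-masking values are 0.01% and 3%.

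These figures cover the count limb alone, not the pattern limb or the related-SAE limb.

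**The case against.** The strongest reply is that need is a clinical judgement. The saline is labelled maintenance, and a clinician can still decide that a nauseated participant needs more than maintenance. Milder dehydration under routine fluid may even be a truly milder event under the care given. This stands in part: misgrading is possible, not certain. But a participant taking in little by mouth while receiving 3.0 L a day will seldom show that need, and Table 2 offers no other route to grade 2.

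A second reply is that an article leaves grading instructions to the full protocol. That would answer a complaint about a missing instruction. The point here is that the scale, the infusion and the endpoint threshold are all stated, and they work badly together.

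A third reply is that the consequence is small, and this largely stands. The pattern limb has no grade threshold, any related SAE halts escalation, and the DSMB receives all adult safety data. Vomiting keeps its episode count, and grade 3 nausea can be reached through weight loss. Ondansetron is given before DON and again at 6 h, so true nausea rates may be below those assumed. The children are comatose and Table 3 has no nausea row, so any effect on pediatric dosing is indirect.

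Two stronger readings do not hold. A reader might infer that the running saline would itself be counted as rehydration, inflating grade 2 nausea. The wording does not invite this: fluid scheduled for everyone is not required by anyone's nausea, and that reading would leave grade 1 empty among infused adults. A reader might also infer that section {13} excludes healthy adults from the infusion. It names only the malaria group but does not say that only they receive it, while section {11d} explicitly says all adults. The two passages need aligning, but they do not prove that the groups were treated differently.

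**Conclusion.** The point holds as a minor one. For adults on scheduled saline, the sole criterion between grades 1 and 2 nausea is likely to be pre-empted during the 24-h admission. Nausea with reduced intake in that window may therefore be recorded as grade 1 and left out of the primary endpoint, its nausea component and the count limb. Days 2 to 14 are not affected.

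The size is unknown. The illustration shows only that it could matter under some assumed rates: at 40% nausea, masking a quarter of true grade 2 cases halves the chance of meeting the count limb, from 12% to 6%. It is not evidence that this happened. The documents do not support a claim that escalation was unsafe. What is weakened is how far a low grade 2–3 nausea rate, or a flat one across doses, can be read as good tolerability.

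**What to change.** 1. **Adults already enrolled under version 1.7.** Leave the recorded grades as they are. By dose and adult group, report the primary endpoint as graded. Beside it, give the number of participants with an event when any first-24-h nausea with reduced oral intake counts as grade 2, labelled as an upper bound. Count participants, so that someone who already has another grade 2–3 event is not counted twice.
2. **Any later adult dosing.** Define grade 2 nausea by degree of oral intake, independent of the scheduled infusion.
3. **Infusion.** State which adult groups received the saline, and align sections {11d} and {13}.

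Cost: one tabulation from existing records, one grading sentence and one clarification. Section {22} says AE records hold the event description, onset date and severity. Table 2's grade 1 already implies reduced intake, so no new data or regrading is needed. Downside: the sensitivity count removes the distinction between grades 1 and 2 for first-24-h nausea. It overstates grade 2 nausea and must not be read as an estimate.

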#### Pediatric

Pediatric participants receive a premedication dose of ondansetron 0.15 mg/kg (maximum 5.0 mg) IV, administered 30 min before DON and repeated at 8 and 16 h after DON or placebo treatment. While on the clinical unit, all pediatric participants receive standard of care antimalarial treatment. IV artesunate is administered according to the current national treatment guidelines upon admission, at 12 and 24 h post-admission, and once a day thereafter until the child is able to take oral medications or tolerate nasogastric antimalarial administration, or for a total of 5 days, whichever comes first. After the child is able to take medications enterally, they are prescribed Co-Artem® (a fixed dose combination tablet containing artemether, 20 mg and lumefantrine, 120 mg) twice daily for 3 days.

All pediatric patients require a nasogastric tube and feeds are held for the first 24 h post-DON administration to decrease the risk of aspiration while comatose. Other supportive treatment for all participants is provided as clinically indicated.

### Provisions for post-trial care {30}

Should study participants become ill during trial follow-up and present to the study site, immediate medical treatment is provided by the study team and referred for appropriate health care if needed. Clinical trial insurance was obtained for all participants enrolled in this trial. Participants are informed of the existence of the insurance.

### Outcomes {12}

Primary and secondary endpoints in adult and pediatric cohorts assess safety and tolerability. As the risk–benefit profile and study designs vary between healthy and uncomplicated malaria participants and CM participant cohorts, we have delineated the safety endpoints and time of measurements relative to the study design and risk–benefit profile for each cohort.

### Primary endpoints

In adult participants, the primary endpoint is any grade 2 or 3 AE or SAE in the 14 days after DON administration. In pediatric participants with CM, the primary endpoint includes any SAEs at any time within 14 days after DON administration. The list of solicited AEs is based on known AEs from previous DON trials. All other AEs are documented as unsolicited events. AE grading (Tables 2 and 3) was adapted from the National Institute of Allergy and Immunology (NIAID) Division of AIDS (DAIDS) toxicity tables criteria [43].

**Table 2 Tab2:** Toxicity grading scales for adult participants

Parameter	Grade 1	Grade 2	Grade 3
White blood cells (10^3^/μL)	2.0 to 2.39 if normal baseline 35% reduction from baseline, if abnormal baseline	1.5 to 1.99 if normal baseline 50% reduction from baseline, if abnormal baseline	Less than 1.5 if normal baseline 65% reduction from baseline, if abnormal baseline
Hemoglobin (g/dL)			
Healthy male Normal baseline	10 to 10.9	9 to < 10	< 9
Healthy female Normal baseline	9.5 to 10.4	8.5 to < 9.5	< 8.5
Uncomplicated malaria^a^	35% reduction from baseline	50% reduction from baseline	65% reduction from baseline
Platelets (10^3^/μL)	100 to 116 if normal baseline 35% reduction from baseline, if abnormal baseline	50 to 99 if normal baseline 50% reduction from baseline, if abnormal baseline	< 50 if normal baseline65% reduction from baseline, if abnormal baseline
Serum creatinine	1.1–1.3 × ULN	> 1.3 to 1.8 × ULN	> 1.8 × ULN
Serum SGOT	1.25 to < 2.5 × ULN if normal baseline	2.5 to < 5.0 × ULN if normal baseline	≥ 5.0 × ULN if normal baseline
	35% increase from baseline, if abnormal baseline	50% increase from baseline, if abnormal baseline	65% increase from baseline, if abnormal baseline
Diarrhea	3 or more loose stools in 24 h, treated with dietary changes	6 or more loose stools in 24 h requiring IV rehydration for clinical stabilization, resolving within 36 h	≥ 6 loose stools in 24 h requiring IV rehydration for clinical stabilization, not resolving within 36 h
Gastrointestinal bleeding	Coffee ground emesis or positive stool hemoccult or frank bleeding with < 10% decrease in hematocrit/PCV	Coffee ground emesis or positive stool hemoccult or frank bleeding with a ≥ 10% decrease in hematocrit/PCV not requiring transfusion	Coffee ground emesis or positive stool hemoccult or frank bleeding with a ≥ 10% decrease in hematocrit/ PCV requiring transfusion
Mucositis	Erythema of the mucosa	Patchy pseudomembranes or ulcerations	Confluent pseudomembranes or ulcerations OR mucosal bleeding with minor trauma
Hematuria	Microscopic hematuria	Frank hematuria with normal serum creatinine (within the normal range for age)	Frank hematuria with elevated (outside of the normal range for age) serum creatinine
Nausea	Nausea with decreased oral intake not requiring intravenous rehydration	Nausea with decrease oral intake requiring intravenous rehydration	Inadequate oral fluid and caloric intake with resulting hypotension or weight loss
Vomiting	1–3 episodes in 24 h with no or mild dehydration	4–6 episodes in 24 h or any amount with moderate dehydration requiring intensive intravenous rehydration	> 6 episodes in 24 h or any amount of vomiting resulting in persistent hypotension

*ULN* Upper limit of normal, *SGOT* Serum glutamic-oxaloacetic transaminase

^a^Platelets and hemoglobin are expected to be abnormal in participants with uncomplicated malaria

**Table 3 Tab3:** Toxicity grading scales for pediatric participants

Parameter	Grade 1	Grade 2	Grade 3
White blood cells (10^3^/μL)	2.0–2.39 if normal baseline	1.5–1.99 if normal baseline	< 1.5 if normal baseline
			65% reduction from baseline, if abnormal baseline
	35% reduction from baseline, if abnormal baseline	50% reduction from baseline, if abnormal baseline	
Hematocrit (PCV)	Not applicable as ongoing anemia and need for blood transfusions not unexpected		
Platelets (10^3^/μL)	100–116 if normal baseline	50–99 if normal baseline	< 50 if normal baseline
		50% reduction from baseline if abnormal baseline	65% reduction from baseline, if abnormal baseline
	35% reduction from baseline, if abnormal baseline		
Serum creatinine	35% increase from baseline	50% increase from baseline	65% increase from baseline
Serum SGOT	1.25 to < 2.5 × ULN if normal baseline	2.5 to < 5.0 × ULN if normal baseline	≥ 5.0 × ULN if normal baseline
			65% increase from baseline, if abnormal baseline
		50% increase from baseline, if abnormal baseline	
	35% increase from baseline, if abnormal baseline		
Serum glucose	Not applicable: hypoglycemia during first 72 h of admission with CM is not unexpected and is closely monitored		
Serum lactate	Not applicable: hyperlactatemia during first 72 h of admission with CM is not unexpected and is closely monitored		
Diarrhea	3 or more loose stools in 24 h, treated with dietary changes	6 or more loose stools in 24 h requiring IV rehydration for clinical stabilization, resolving within 36 h	6 or more loose stools in 24 h requiring IV rehydration for clinical stabilization, not resolving within 36 h
Gastrointestinal bleeding	Coffee ground emesis or positive stool hemoccult or frank bleeding with < 10% decrease in hematocrit/PCV	Coffee ground emesis or positive stool hemoccult or frank bleeding with a ≥ 10% decrease in hematocrit/PCV not requiring transfusion	Coffee ground emesis or positive stool hemoccult or frank bleeding with a ≥ 10% decrease in hematocrit/PCV requiring transfusion
Mucositis	Erythema of the mucosa	Patchy pseudomembranes or ulcerations	Confluent pseudomembranes or ulcerations OR mucosal bleeding with minor trauma
Hematuria	Microscopic hematuria	Frank hematuria with normal serum creatinine (within the normal range for age)	Frank hematuria with abnormally elevated (outside of the normal range for age) serum creatinine
Vomiting	1–3 episodes in 24 h with no or mild dehydration	4–6 episodes in 24 h or any amount of vomiting with moderate dehydration requiring intensive intravenous rehydration	More than 6 episodes in 24 h resulting in persistent hypotension

Laboratory parameters impacted by cerebral malaria are expected to be disordered prior to DON administration

*ULN* Upper limit of normal, *SGOT* Serum glutamic-oxaloacetic transaminase, *PCV* Packed cell volume

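### Table 2's grading rules for normal and abnormal baselines do not fit together for WBC, platelets and SGOT, so adult grades are not ordered by severity across the grade 1/2 boundary that defines the primary endpoint

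*Protocol article*

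**What the plan says.** The counting rule is in *Primary endpoints*: "In adult participants, the primary endpoint is any grade 2 or 3 AE or SAE in the 14 days after DON administration". The step from grade 1 to grade 2 is therefore what turns a laboratory change into an endpoint event.

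Table 2 sets the grades. Three rows switch scale according to baseline status:

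- **Platelets (10^3/μL).** Grade 1 is "100 to 116 if normal baseline 35% reduction from baseline, if abnormal baseline". Grade 2 is "50 to 99 if normal baseline 50% reduction from baseline, if abnormal baseline". Grade 3 is below 50 from a normal baseline, or a 65% fall from an abnormal one.
- **WBC (10^3/μL).** From a normal baseline, grades 1 and 2 are 2.0 to 2.39 and 1.5 to 1.99. From an abnormal one they are falls of 35% and 50%. Grade 3 is "Less than 1.5 if normal baseline 65% reduction from baseline, if abnormal baseline".
- **SGOT.** From a normal baseline, grades 1, 2 and 3 start at 1.25, 2.5 and 5.0 x ULN. From an abnormal one they are rises of 35%, 50% and 65%; the grade 3 entry is "65% increase from baseline, if abnormal baseline".

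The table does not say what makes a baseline abnormal, or whether high and low values both qualify. Its footnote says that abnormal platelets and hemoglobin are to be expected in adults with uncomplicated malaria. The adult escalation rule (*Criteria for discontinuing or modifying allocated interventions {11b}*, Adults) counts related grade 2 and 3 events on the same scale.

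**The concern.** Grading against baseline is a sensible choice when baseline values are disordered. The difficulty is that the percent branch carries no absolute anchor and the absolute branch takes no account of change. Two adults on either side of the normal limit can therefore be ranked in the wrong order, and the reversals straddle the grade at which events begin to count.

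The rows involved matter for this drug: the *Discussion* lists thrombocytopenia, leukopenia and raised aspartate transaminase among the potential risks. If falls in platelets are under-counted in the malaria group and small SGOT rises are over-counted, the adult event rates by group and dose partly reflect which branch each participant was on. Those adult data are among the inputs to the pediatric doses (*Trial design {8}*).

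**Working it through.** The plan states no figure for this point, so there is none to reproduce. The check applies Table 2 as printed, reading each percent threshold as 'at least'. All patient values are illustrative; the cut-offs are the table's own.

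**1. SGOT (multiples of ULN)**
- Normal baseline, 1.0 to 2.4: (2.4 − 1.0)/1.0 = +140%. The value lies in 1.25 to <2.5, so grade 1, not counted.
- Abnormal baseline, 1.1 to 1.82: (1.82 − 1.1)/1.1 = +65.5%, so grade 3, counted.
- A 50% rise stays below 2.5 x ULN for any abnormal baseline below 2.5/1.5 = 1.67. A 65% rise stays below it for any baseline below 2.5/1.65 = 1.52. In that second range, grade 3 is reached before a participant with a normal baseline would reach grade 2.
- The error reverses higher up: 4.0 to 5.9 is (5.9 − 4.0)/4.0 = +47.5%, so grade 1, although 5.0 or more is grade 3 from a normal baseline.

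**2. Platelets**
- Normal baseline, 120 to 99: 21/120 = 17.5% fall, grade 2, counted. If normal is taken to start at 150, 150 to 99 (51/150 = 34%) is also grade 2.
- Abnormal baseline, 110 to 56: 54/110 = 49.1% fall, grade 1, not counted. The value 56 lies in the absolute grade 2 band.
- Abnormal baseline, 80 to 41: 39/80 = 48.8% fall, grade 1, not counted. The value 41 lies in the absolute grade 3 band.
- A 50% fall ends below 99 for any baseline below 99/0.5 = 198, and a 65% fall ends below 50 for any baseline below 50/0.35 = 143. Low baselines under 143 are thus graded more leniently at both counted grades.

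**3. WBC**
- If 2.5 is an abnormal baseline, 2.5 to 1.3 is 1.2/2.5 = 48% fall, grade 1, not counted. Below 1.5 is grade 3 from a normal baseline.

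**4. Can noise alone produce SGOT events?** The document gives no within-person variability, so this is an assumption shown over a range. Take a true level of 1.1 x ULN, log-normal variation, an observed baseline above ULN, no drug effect, and the four scheduled post-dose safety draws (12 h, 24 h, day 7, day 14). The simulated chance of at least one rise of 50% or more is:

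| Within-person CV | Chance |
|---|---|
| 10% | 0.04% |
| 15% | 1.3% |
| 20% | 5.3% |
| 25% | 10.5% |
| 30% | 15.7% |

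These chances apply only to participants with a mildly raised baseline, whose share is unknown.

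**5. Escalation rule.** Halting on this count needs at least 5 of 10. Even if all ten in a cohort were such participants and every rise were judged related, the binomial chance of 5 or more is about 0.01% at 5.3% per person and 1.2% at 15.7%.

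**The case against.** The strongest reply is that percent change is deliberate where the baseline is already disordered, and that a condensed article may leave the definition of an abnormal baseline to the full protocol. Both points are fair. Neither cures the SGOT and platelet reversals, which follow from the printed cut-offs whatever the exact limits of normal.

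Several stronger conclusions are tempting, and the document does not support them.

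- **Recovery graded as toxicity.** A reader might infer that a raised WBC settling from 16 to 5.6 (a 65% fall) counts as grade 3. That needs 'abnormal' to include high counts. The row grades reductions and the named risk is leukopenia, so a low-only reading is at least as natural.
- **False SGOT and WBC events piling up in the malaria group.** The footnote expects abnormal platelets and hemoglobin only. For platelets the error runs towards under-counting. Hemoglobin switches by participant group rather than by baseline status and is outside this point.
- **A biased comparison of doses or groups.** No formal healthy-versus-malaria comparison is stated. The four dose cohorts within each group share the same rules, so only chance imbalance in baselines at n = 10 distorts the comparison between doses.
- **Contaminated pediatric results.** Table 3 has the same structure, and its note that "Laboratory parameters impacted by cerebral malaria are expected to be disordered prior to DON administration" makes this inference easy. But the pediatric primary endpoint and halting rule rest on SAEs, and *Interim analyses {21b}* names the primary safety endpoint and exploratory efficacy as informing the later doses.
- **Escalation decisions overturned.** The rule counts related events after a clinician has considered alternative causes, and step 5 shows that SGOT noise alone would very rarely trigger it.

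**Conclusion.** The point stands for the adult primary endpoint. For WBC, platelets and SGOT, Table 2 does not order events by severity across the grade 1/2 boundary. The direction depends on the parameter. Low platelets, and low WBC if treated as abnormal, are under-graded. Mildly raised SGOT is over-graded and markedly raised SGOT can be under-graded. The platelet problem is the most likely to occur, because the table itself anticipates abnormal baselines in the malaria group of 40 adults.

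The size at endpoint level cannot be computed: the document gives no baseline distributions and no limits of normal. The existence of the reversals rests only on the printed cut-offs. The noise figures rest on an assumed CV and should not be read as an estimate of miscounted adults.

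**What to change.** Reconcile the two branches in Table 2, and state what an abnormal baseline is, parameter by parameter, including its direction.

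Keep the as-written grading as the reported adult primary result. *Trial status* speaks of adult enrollment in the past tense and this part was open-label, so replacing the grading now would redefine the endpoint after data collection.

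Add a sensitivity re-grading of the stored adult values for these three parameters:

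1. Grade the baseline and every post-dose value on the table's own absolute bands, whatever the baseline status.
2. Count a grade 2 or 3 event only when the post-dose grade exceeds the baseline grade.
3. Report the adult primary endpoint both ways, by participant group and dose.

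On the examples above, platelets 110 to 56 (grade 1 to 2) and 80 to 41 (2 to 3), WBC 2.5 to 1.3 (0 to 3) and SGOT 4.0 to 5.9 (2 to 3) become counted. SGOT 1.1 to 1.82 (0 to 1) drops out. No new threshold is needed. Simply requiring both the percent change and the absolute band would leave the SGOT 4.0 to 5.9 case uncounted.

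The cost is a table clarification and a short program on data already held. The downside is that worsening within one band is missed in the sensitivity version: SGOT 2.5 to 4.9 (2.4/2.5 = +96%) is grade 3 as written, but stays in the grade 2 band and is not counted. Two sets of counts must also be shown and explained.
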